#### Quality control

2.3.9

A three-tier quality control system will be established to ensure data quality:

First-tier: Research coordinators at each center will perform initial verification of data completeness and accuracy. They will review all CRFs against source documents before submission. Second-tier: Independent quality control supervisors will conduct monthly random checks of 10% of all entered data, comparing them with source documents. Any discrepancies identified will be resolved through queries to the research coordinators. Third-tier: The central study team will perform quarterly systematic reviews of the database, focusing on: (1) Data consistency across centers; (2) Protocol compliance; (3) Follow-up completeness; (4) Logical relationships between variables; (5) Outlier detection. Regular training sessions will be conducted for all research staff to standardize data collection procedures. Standard operating procedures (SOPs) will be established for each aspect of data collection and management. The study platform will generate monthly quality reports highlighting potential issues for immediate attention.

An independent data monitoring committee will oversee the overall data quality and safety. Site visits will be conducted every six months to verify source data and ensure protocol adherence. Any protocol violations or systematic errors identified will trigger immediate corrective actions and additional staff training if necessary.

#### Statistical analysis

2.3.10

All statistical analyses will be performed using R version 4.0.0 and STATA version 16.0 software. Descriptive statistics will be presented as means ± standard deviations or medians (interquartile ranges) for continuous variables, and frequencies (percentages) for categorical variables. Incidence rates will be described using cumulative incidence and incidence density.

To enhance the biological validity of TCM classification, this study employs multi-omics approaches to validate associations between TCM syndrome differentiation and CRA. Metagenomics analysis utilizes high-throughput sequencing platforms to detect fecal 16S rRNA genes, employing bioinformatic tools for species identification and pathway analysis, with concurrent measurement of α and β diversity indices. Metabolomics analysis targets plasma and other biological specimens using liquid chromatography-mass spectrometry for non-targeted detection, while conducting targeted analysis of TCM-relevant metabolites, with data processed through specialized analytical platforms. Finally, biological network tools are applied to construct microbiome-metabolome interaction networks, exploring their associations with TCM syndrome patterns.

For inferential analysis, the Kaplan-Meier method will be used to estimate the cumulative incidence of CRA detection and cancer occurrence (16). Cox proportional hazards regression models (17) will be employed to analyze risk factors affecting outcomes, while competing risk models (18) will be utilized to evaluate interactions between different outcomes. Time-dependent Cox models will be used to assess the impact of dynamic risk factors on prognosis (19).

Subgroup analyses will be conducted by stratifying patients according to age, gender, and baseline adenoma characteristics. Interaction terms will be used to assess heterogeneity between subgroups. For sensitivity analyses, multiple imputation methods will be employed for handling missing data, and complete case analysis will be compared with intention-to-treat analysis. Result estimates will be assessed at different follow-up time points.

For continuous variables following normal distribution, independent sample t-tests will be used to compare differences between groups. For categorical variables, chi-square tests or Fisher’s exact tests will be applied as appropriate. Multivariate analysis will incorporate instrumental variables, multiple linear models, logistic regression (20), and Cox regression to explore the relationship between TCM syndromes and patient outcomes (21).

An interim analysis will be conducted when 50% of the target sample size is achieved. All statistical tests will be two-sided, with P<0.05 considered statistically significant.

Beyond determining the total sample size, we further considered the statistical power for key subgroup analyses. Based on prior literature reviews (22), the expected distribution of major TCM syndrome types in the study population is as follows: the “Dampness-Heat Accumulation” syndrome (dominant type) accounts for 28.70%, while the “Spleen Deficiency with Dampness Retention” and “Spleen Qi Deficiency” syndromes (major subgroups) account for 9.18% and 8.06%, respectively. With a total sample size of 15,000 participants, approximately 4,305 cases are expected to be classified under “Dampness-Heat Accumulation,” 1,377 under “Spleen Deficiency with Dampness Retention,” and 1,212 under “Spleen Qi Deficiency.” This sample allocation accurately matches the anticipated syndrome distribution, enabling the investigation of outcomes such as adenoma recurrence and malignant transformation, and fully meets the statistical requirements for comparative analyses among different TCM syndrome types.

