#### Outcomes

2.3.5

The primary outcomes of this prospective multicenter cohort study comprise two main endpoints: CRC occurence and CRA recurrence is defined as any histologically confirmed CRA detected during scheduled follow-up colonoscopy examinations at 12, 24, 36, 48, and 60 months after baseline. Each adenoma will be systematically evaluated according to standardized criteria, including anatomical location within the colorectum, maximum diameter measured by open biopsy forceps, and total number of lesions. Histological classification will follow the World Health Organization criteria.

For CRC occurence, the outcome is defined as any histologically confirmed CRC diagnosed during the follow-up period. Each case will undergo comprehensive assessment including TNM staging classification according to the American Joint Committee on Cancer (AJCC) 8th edition, detailed histological type and grade evaluation, and precise documentation of tumor location and size. To ensure data quality and consistency, all colonoscopy procedures will be performed by certified endoscopists following standardized protocols, and all pathological specimens will undergo centralized review by experienced gastrointestinal pathologists.

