#### Sample size

2.3.6

For this multicenter prospective cohort study, we calculated the sample size based on two primary outcomes: CRA recurrence and CRC occurrence. According to previous studies, the detection rate of CRA ranges from 15%-30% during 3-year follow-up and reaches 48%-68% during 5-year follow-up, while the annual incidence of CRC among adenoma patients is approximately 0.2%-0.5%.

We employed the cohort study sample size calculation formula N = (Zα/2 + Zβ)² × P(1-P)/d², where Zα/2 = 1.96 (α = 0.05, two-sided), Zβ = 1.28 (statistical power = 90%), and d represents the acceptable margin of error. Two primary outcomes guided our sample size determination: CRA recurrence and malignant transformation.

For the adenoma recurrence outcome, we considered the 5-year cumulative recurrence rate ranging from 48% to 68%, with a median of 58%. Using an absolute error of 2%, the minimum sample size calculation yielded 6,394 cases. After accounting for a 20% potential loss to follow-up, the adjusted sample size was 7,993 cases.

Regarding malignant transformation, the occurrence rate was estimated between 0.2% and 0.5%, with a median of 0.35%. We applied a relative error of 50% (0.175%), which resulted in a minimum sample size of 11,970 cases. Incorporating the 20% follow-up loss adjustment, the final target became 14,963 cases.

Considering the statistical requirements, research resources, and the need for robust analysis, we ultimately set the total enrollment target at 15,000 participants. This approach ensures adequate statistical power to detect clinically meaningful differences while providing comprehensive insights into CRA progression and cancer risk. This sample size ensures adequate statistical power to detect clinically meaningful differences in both primary outcomes while accounting for potential loss to follow-up. An interim analysis will be conducted when 50% of the target sample size is achieved.

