## Discussion

This study aims to establish China’s first large-scale, multicenter integrated traditional Chinese and Western medicine (TCM-WM) cohort study for CRA. Through standardized data collection and biobank establishment, we explore the relationship between TCM syndromes and disease prognosis, providing evidence-based medical evidence for integrated TCM-WM treatment approaches.

CRA are crucial precancerous lesions, with approximately 85-90% of CRC developing through the adenoma-carcinoma sequence (23). Global research data indicates that the detection rate of CRA in the general population is approximately 20-30%, with increasing incidence trends (24). More importantly, the recurrence rate after endoscopic polypectomy remains high, imposing substantial health and economic burdens on patients. Although colonoscopy and polypectomy are currently the gold standard for CRC prevention, effective interventions for preventing adenoma recurrence are still lacking (25).

This study not only examines the relationship between TCM syndromes and disease prognosis but further investigates the molecular mechanisms underlying TCM therapies for CRA, providing comprehensive evidence-based medical support. Research demonstrates that Shenbaijiedu formula modulates immunosuppressive dendritic cell differentiation through the TMEM131-TNF signaling pathway, inhibiting malignant transformation of CRA, with its mechanism precisely elucidated via single-cell transcriptomic sequencing (26). Additionally, multicenter, randomized, double-blind, placebo-controlled clinical trials of Shenbai granules (containing Sophora flavescens, Hedyotis diffusa, Codonopsis pilosula, and stir-fried Atractylodes macrocephala) confirm that this formulation significantly reduces post-operative recurrence rates in CRA patients and decreases CRC risk. Various extracts from these constituent herbs exert their effects through multiple pathways, including signal transduction intervention, anti-inflammatory actions, immune regulation, and gut microbiota modulation (27).

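### Kaplan-Meier is named as the estimator of cumulative incidence and no competing-risk method is assigned to death, so recurrence risk will be modestly overstated

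*Protocol article*

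**What the plan says.** Section 2.3.10 of the protocol article names the estimator for both primary outcomes: "the Kaplan-Meier method will be used to estimate the cumulative incidence of CRA detection and cancer occurrence". It plans Cox models for risk factors and time-dependent Cox models for risk factors that change. It then adds that "competing risk models (18) will be utilized to evaluate interactions between different outcomes". No competing event is named, and the article does not mention death as an outcome, a competing event or a reason for censoring.

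The outcomes are recurrence and CRC; the Sample size section (2.3.6) says "we calculated the sample size based on two primary outcomes: CRA recurrence and CRC occurrence". For CRC, the Outcomes section (2.3.5) says "the outcome is defined as any histologically confirmed CRC diagnosed during the follow-up period". That wording is not limited to cancers that precede a recurrence.

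The Study population section (2.2) admits adults from 18 years with no upper age limit, and follow-up lasts 5 years.

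**The concern.** Cumulative incidence is the proportion of the cohort who will have had the event by a given time. A patient who dies first never has it. Kaplan-Meier with deaths censored treats the dead as if they carried the same future risk as those still followed, so its complement exceeds that proportion whenever there are deaths. In adults of any age followed for 5 years, some deaths must be expected.

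The competing-risk sentence does not repair this, because it gives those models another task. That task is itself unclear: recurrence does not prevent CRC and, since the Discussion describes CRC as arising "with approximately 85-90% of CRC developing through the adenoma-carcinoma sequence", may be a step towards it.

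At stake is the accuracy of the reported absolute risks. The bias does not shrink as enrolment grows. Because mortality rises with age, it would also differ between the age subgroups that the plan intends to compare.

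**Working it through.** **Inputs from the article (2.3.6).** Recurrence: "we considered the 5-year cumulative recurrence rate ranging from 48% to 68%, with a median of 58" per cent, with an absolute error of 2%. CRC: one sentence says "the annual incidence of CRC among adenoma patients is approximately 0.2%-0.5" per cent; the calculation then uses 0.35% without a time unit. Relative error for CRC 50%; loss 20%; z values 1.96 and 1.28; follow-up 5 years.

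**The plan's own figures.** N = (1.96 + 1.28)² × P(1 − P)/d².

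- Recurrence: 10.4976 × 0.58 × 0.42 / 0.02² = 6,393.04, rounded up to 6,394 as stated; 6,394/0.8 = 7,993 as stated.
- CRC: 10.4976 × 0.0035 × 0.9965 / 0.00175² = 11,955, against 11,970 stated (0.1% apart); 11,970/0.8 = 14,963 as stated.

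These figures do not depend on the estimator. They matter here only as the source of the 2-point margin.

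**Recurrence.** Assume constant hazards over T = 5 years. If Kaplan-Meier gives 58%, the recurrence hazard is λ = −ln(0.42)/5 = 0.1735 per year. For an assumed 5-year mortality m, μ = −ln(1 − m)/5. The cumulative incidence with death competing is λ/(λ + μ) × [1 − exp(−5(λ + μ))].

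| Assumed 5-year mortality | μ per year | Cumulative incidence | Kaplan-Meier too high by |
|---|---|---|---|
| 3% | 0.00609 | 0.9661 × 0.5926 = 57.25% | 0.75 points |
| 5% | 0.01026 | 0.9442 × 0.6010 = 56.74% | 1.26 points |
| 10% | 0.02107 | 0.8917 × 0.6220 = 55.46% | 2.54 points |

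Over a wider assumed range of 0.2% to 3% deaths per year, the overstatement at 58% runs from 0.25 to 3.56 points (0.4% to 6.5% relative). At 1% per year it is 1.05, 1.22 and 1.36 points for recurrence of 48%, 58% and 68%.

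For comparison, with 15,000 × 0.8 = 12,000 followed, a simple 95% half-width at 58% is 1.96 × √(0.58 × 0.42/12,000) = 0.9 points.

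**CRC.** At 0.35% per year, Kaplan-Meier gives 1 − exp(−0.0175) = 1.735%. The same formula gives 1.726% at 0.2% deaths per year and 1.611% at 3%. The overstatement is 0.01 to 0.12 points, or 0.5% to 7.7% relative. If 0.35% is instead the 5-year risk, it is 0.002 to 0.025 points, with the same relative size.

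**Conditional check: what if recurrence were coded as competing with CRC?** With recurrence hazard r, CRC hazard h = 0.0035 and the same CRC hazard before and after recurrence, CRC as a first event is h/(h + r) × [1 − exp(−5(h + r))]. At 58% recurrence this is 0.0035/0.1770 × (1 − exp(−0.885)) = 1.161%, against 1.735% in all. The uncounted share is 1 − 1.161/1.735 = 33%. At 48% and 68% recurrence it is about 27% and 40%.

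**The case against.** A reader might infer something stronger: that the competing-risk models set recurrence against CRC, so that cancers following a recurrence are thrown away. Recurrence and CRC are the only outcomes defined, so the first step is a natural guess, but the documents do not support the conclusion. Nowhere are recurrences coded as competing events for CRC, and nowhere does CRC follow-up stop at recurrence. Section 2.3.5 counts any CRC during follow-up, so the planned Kaplan-Meier and Cox analyses of CRC would keep those cancers. The competing-risk models are an addition to them. The sentence could equally mean CRC competing with recurrence, which is legitimate if a cancer ends surveillance for adenomas. The one-third loss is therefore only what an unstated coding would produce.

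Other objections have weight. This is a journal article; coding of events and individual form items may sit in a fuller document. The lack of a death row in Table 1 does not show that deaths go unrecorded, since the Data collection section (2.3.7) plans documented reasons for missing data and three telephone attempts before a loss is declared. The article also does not say that Kaplan-Meier estimates feed the prediction model. The bias is modest: at 3% and 5% mortality it is below the 2-point margin, and for CRC it is minor beside the planned 50% relative error.

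What remains is that the article does name an estimator for cumulative incidence, and does give competing-risk models a task other than death. That is a stated choice rather than an omitted detail.

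**Conclusion.** The point holds in a limited form. Kaplan-Meier with deaths censored overstates the cumulative incidence of both primary outcomes, and nothing in section 2.3.10 corrects for it. For recurrence at 58% the excess is about 0.8, 1.3 or 2.5 points at 5-year mortality of 3%, 5% or 10%. Only the last exceeds the planned margin, but at 5% the bias is already larger than the sampling half-width of 0.9 points. For CRC it is negligible in absolute terms.

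These sizes assume constant hazards, censoring at death (usual practice, though the article does not say so), and a death rate that is nowhere given. They ignore that recurrence is seen only at colonoscopy. The direction of the bias does not depend on the assumed death rate; its size does.

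**What to change.** Replace Kaplan-Meier by the Aalen-Johansen estimator for cumulative incidence. For CRC, take death as the competing event. For recurrence, take death, and also CRC if it ends surveillance for recurrence. Keep the planned Cox models and describe them as cause-specific hazards.

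Reword the competing-risk sentence to name the competing events. State that CRC is counted regardless of an earlier recurrence, in line with section 2.3.5. Study the link from recurrence to CRC with an illness-death model, or with recurrence as a time-dependent covariate in the time-dependent Cox models already planned.

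The cost is a few sentences of analysis text. Reported incidence will be slightly lower, and a date of death must be available from the planned follow-up contacts. It is best to confirm now that deaths are recorded separately from other losses.

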**Methods and analysis:**

This is a multicenter prospective cohort study. A total of 15,000 patients with colonoscopy-confirmed colorectal adenomas will be recruited from 12 tertiary hospitals in China. At baseline, TCM characteristics (syndromes, constitution, tongue and pulse features), endoscopic findings, and biological samples (tongue coating, saliva, stool, blood, tissue) will be collected. The participants will be followed up for 5 years with risk-stratified standardized colonoscopy intervals. The primary outcomes are adenoma recurrence and CRC occurrence. The secondary outcomes include identifying risk factors and developing a predictive model. Multivariable logistic regression, Cox models, and mixed-effects models will be used for data analysis. A comprehensive biobank will be established to support future mechanistic studies.

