#### Follow-up schedule and procedures

2.3.3

Follow-up examinations will be conducted at 12, 24, 36, 48, and 60 months after enrollment. During each follow-up visit:

Clinical examination encompassed comprehensive history-taking (with emphasis on gastrointestinal symptoms and treatment-related complications) and thorough physical examination. Follow-up assessments utilized structured questionnaires combined with medication verification to document patients’ TCM usage over the preceding 6 months, recorded in the ‘Follow-up Medication Record Form’ For patients reporting TCM use, TCM diagnostic data collection was immediately suspended, and patients were instructed to discontinue all TCM preparations for 1 week before returning for morning fasting reassessment. This protocol enabled dual verification through baseline-versus-follow-up data comparison and post-cessation sign monitoring, allowing differentiation between treatment-induced changes and genuine pathological manifestations.Colonoscopy will be performed according to standard clinical practices to detect adenoma recurrence (**Table 2**). The timing and frequency may be adjusted based on baseline findings according to guidelines for adenoma surveillance (14, 15).Updated laboratory tests similar to baseline will be performed to monitor changes and identify potential biomarkers of adenoma recurrence or progression.TCM syndrome evaluation will be repeated to track changes in syndrome patterns and their potential association with disease progression.Risk factor assessment will be updated, including changes in lifestyle factors (smoking, alcohol consumption, diet, physical activity).Treatment information will be collected, documenting both Western medical interventions and TCM treatments.

**Table 2 T2:** Follow-up intervals after endoscopic resection of colorectal polyps or adenomas.

Initial colonoscopy findings	Colonoscopy follow-up interval (Years)
No polyps	3–5
Hyperplastic polyp in rectum or sigmoid(diameter <10 mm)	2–3
1–2 tubular adenomas (diameter < 10 mm)	1–3
3–10 tubular adenomas	1–2
≥ 1 tubular adenoma (diameter ≥ 10 mm)	1–2
≥ 1 villous adenoma	1–2
Adenoma with high-grade intraepithelial neoplasia	1–2
Serrated lesion < 10 mm without intraepithelial neoplasia	2–3
Serrated lesion > 10 mm without intraepithelial neoplasia	1–2

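### Adenoma recurrence is seen only at colonoscopy, the article contradicts itself on when colonoscopy happens, and if timing follows baseline findings the named models bias the estimates for baseline adenoma features

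*Protocol article*

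**What the plan says.** Two accounts of colonoscopy timing stand side by side.

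- **Annual for everyone.** Section 2.3.5 defines recurrence as "any histologically confirmed CRA detected during scheduled follow-up colonoscopy examinations at 12, 24, 36, 48, and 60 months after baseline". Table 1 (section 2.3.2) ticks colonoscopy, pathology and recurrence assessment at each of those five visits.
- **Set by baseline findings.** The abstract says patients will be "followed up for 5 years with risk-stratified standardized colonoscopy intervals". Section 2.3.3 adds: "The timing and frequency may be adjusted based on baseline findings according to guidelines for adenoma surveillance". Table 2 gives 1–3 years for one or two small tubular adenomas, and 1–2 years for 3–10 tubular adenomas, any of 10 mm or more, villous histology or high-grade neoplasia. New symptoms can also bring a colonoscopy forward.

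For analysis, section 2.3.10 names Kaplan-Meier for the cumulative incidence of adenoma detection, and "Cox proportional hazards regression models (17) will be employed to analyze risk factors affecting outcomes". It also lists "logistic regression (20), and Cox regression to explore the relationship between TCM syndromes and patient outcomes". Baseline adenoma characteristics are subgroup variables. The section describes no model as interval-censored or as taking account of the examination schedule, and it gives no censoring rule.

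**The concern.** A recurrent adenoma is usually silent. All that is known is that it arose between the last clear colonoscopy and the first positive one. Kaplan-Meier and ordinary Cox treat the detection date as the event date, and logistic regression treats not detected as not recurred. Comparisons made this way are fair only if the groups are examined equally often.

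Under Table 2 they need not be. Adenoma number, size and histology are risk factors under study, and they also decide how soon the outcome is looked for. Their estimates would then mix biology with surveillance. The 5-year recurrence rate would also be understated wherever the last colonoscopy falls well before month 60. Table 1 adds a practical risk: recurrence is assessed every year, so a visit without colonoscopy could be recorded as recurrence-free.

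**Working it through.** **Inputs from the article.** Five-year recurrence of 58% is the midpoint of 48% and 68% (section 2.3.6). The intervals come from Table 2.

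**The plan's own figure.** (1.96 + 1.28)² × 0.58 × 0.42 / 0.02² = 6,393.04, against 6,394 stated. It reproduces. The point does not rest on it, but it shows that N was set for an absolute error of 2 percentage points.

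**Assumptions not in the article.** Constant hazard, perfect attendance, perfect colonoscopy sensitivity, a fixed schedule per group, half the patients higher-risk, and a true hazard ratio of 1.

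**Step 1: detectable recurrence.** Hazard = −ln(0.42)/5 = 0.1735 per year. The proportion detectable by the last colonoscopy at year t is 1 − exp(−0.1735 t):

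- t = 3: 40.6%
- t = 4: 50.0%
- t = 5: 58.0%

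If the last colonoscopy is at year 3 or 4, detected recurrence falls short of 58% by 17.4 or 8.0 points. Kaplan-Meier carried to month 60 inherits that shortfall.

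**Step 2: odds ratio for ever detected.** The odds are 0.580/0.420 = 1.381 (last examination at year 5), 0.5004/0.4996 = 1.002 (year 4) and 0.4058/0.5942 = 0.683 (year 3). The ratios of these give the odds-ratio column below.

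**Step 3: ordinary Cox.** Simulation of 12,000 patients, five replicates, Efron ties. Each recurrence is detected at the first colonoscopy after onset.

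| Higher-risk examined | Lower-risk examined | HR, censored at last colonoscopy | HR, censored at month 60 | OR |
|---|---|---|---|---|
| yearly | yearly | 1.00 | 1.00 | 1.00 |
| yearly | year 3 only | 1.20 | 1.71 | 1.381/0.683 = 2.02 |
| yearly | years 2, 4 | 1.10 | 1.27 | 1.381/1.002 = 1.38 |
| yearly | years 3, 5 | 1.17 | 1.17 | 1.00 |
| years 2, 4 | year 3 only | 0.82 | 1.36 | 1.002/0.683 = 1.47 |
| years 2, 4 | yearly | 0.92 | 0.80 | 1.002/1.381 = 0.73 |

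The true value is 1 throughout. Repeat runs differ by about 0.02 to 0.03. A variant with 40% higher-risk patients and Breslow ties gave 1.83 where this table has 1.71, so the upper end also depends on set-up.

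**Step 4: does an interval-censored model remove it?** An interval-censored exponential likelihood on the same data returned 0.99 to 1.01 in every row. With a true hazard ratio of 1.5 and intervals of 1 vs 2, 1 vs 3 or 2 vs 3 years, it returned 1.51 to 1.53. Ordinary Cox ranged from 1.37 to 2.65 over the same schedules and both censoring rules.

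**Step 5: a null TCM factor correlated with baseline risk.** Assumed prevalence is 40% in higher-risk and 21% in lower-risk patients, examined every 1 vs 3 years. Censored at the last colonoscopy, the Cox hazard ratio was 1.05 unadjusted and 1.01 adjusted for risk group. Censored at month 60, a repeat run gave 1.13 unadjusted and 0.99 adjusted.

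**The case against.** The strongest reply is that the bias needs unequal examination. The outcome definition and Table 1 both say annual, section 2.3.3 says only that timing may be adjusted, and under annual colonoscopy the spurious effect disappears. That is correct. But the abstract presents risk-stratified intervals as the design and Table 2 tabulates them, so the annual reading cannot be taken as settled.

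A second reply is that this is a condensed article, and that interval censoring and the censoring rule could sit in an analysis plan that is not shown. That stands as regards the missing rule, whose absence is not held against the article. It does not answer the contradiction over when a primary outcome is ascertained. Nor does it change that the methods actually named treat detection as the event.

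Three stronger readings are tempting but not supported:

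- **That the bias always runs away from the null.** Table 2's ranges overlap (1–3 and 1–2 years). Schedules compatible with it give hazard ratios below 1 as well as above.
- **That a hazard ratio near 1.7 is what to expect.** It needs yearly against year-3-only examination and censoring at month 60. Censoring at the last colonoscopy brings it down to about 1.2.
- **That the TCM findings, or the prediction model as a whole, would mainly reflect surveillance.** For a TCM factor the effect is indirect and nearly vanishes on adjustment for baseline risk, and the abstract already plans multivariable models. No calculation here tests the prediction model.

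The point also concerns recurrence more than cancer, since section 2.3.5 counts any cancer diagnosed during follow-up.

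**Conclusion.** The concern holds in a conditional form. The contradiction on colonoscopy timing is certain from the text. If timing follows baseline findings, the named analyses give biased estimates for baseline adenoma features and can understate 5-year recurrence, by 8 to 17 points in the schedules that end at year 4 or year 3. That is well beyond the 2-point error on which N was set. The spurious hazard ratio (about 0.8 to 1.7) and odds ratio (about 0.7 to 2.0) are illustrations under the stated assumptions, not forecasts. Because the sign is not fixed, a reader could not correct for the bias afterwards without the examination dates. It should be settled before analysis, because it affects a primary outcome.

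**What to change.** 1. Reconcile Table 1 and section 2.3.5 with the abstract, section 2.3.3 and Table 2, so that one colonoscopy schedule governs. Which schedule is a clinical decision and is not proposed here.
2. State that a visit without colonoscopy is not scored as recurrence-free.
3. Analyse recurrence from the actual date of every colonoscopy. Place the event between the last negative and first positive examination, and censor at the last negative colonoscopy. Use the Turnbull estimator for cumulative incidence. For risk factors use an interval-censored proportional hazards model, or a discrete-time complementary log-log model over examined intervals.
4. Keep ordinary Cox and logistic regression as sensitivity analyses. Changing the censoring date alone is not enough: in the table above it still leaves hazard ratios of 0.82 to 1.20.
5. Adjust for the baseline adenoma features that set the interval when estimating TCM and other factors. Do not stratify by Table 2 category when those features are themselves the exposure, because the strata would absorb the effect being estimated.

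The cost is wording, slightly more programming and somewhat wider confidence intervals. No new data are needed: colonoscopy reports are already uploaded as source documents (section 2.3.7), and the examination dates can be taken from them.

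### One flat P<0.05 rule covers untargeted omics screens and many syndrome comparisons, and sits beside an interim analysis with no stated purpose

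*Protocol article*

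**What the plan says.** The rule closes the paragraph of section 2.3.10 (Statistical analysis) that sets out the group comparisons and multivariable models: "All statistical tests will be two-sided, with P<0.05 considered statistically significant". It names no exception. The sentence just before it announces the interim analysis, which also appears in section 2.3.6 (Sample size): "An interim analysis will be conducted when 50% of the target sample size is achieved". Neither place gives the purpose of the interim, the quantities to be tested or a boundary.

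The same section describes the analyses that the rule governs:

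- 16S rRNA sequencing of stool, and metabolomics "using liquid chromatography-mass spectrometry for non-targeted detection", followed by interaction networks related to syndrome patterns. The stated aim is to strengthen the biological validity of TCM classification by validating syndrome associations.
- Cox, competing-risk, time-dependent, logistic and instrumental-variable models of risk factors and TCM syndromes, with comparisons among syndrome types.
- Subgroups by age, gender and baseline adenoma characteristics with interaction terms, and estimates at several follow-up times.

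Section 2.3.2 adds genomics and transcriptomics for finding new biomarkers. On outcomes, section 2.3.5 says: "The primary outcomes of this prospective multicenter cohort study comprise two main endpoints". These are adenoma recurrence and colorectal cancer. The article mentions no false-discovery control, test hierarchy or interim boundary.

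**The concern.** A 5% threshold per test is designed for one question. In an untargeted screen it fixes the share of null features that will be called significant, whatever the quality of the data. A list of significant taxa or metabolites for a given syndrome would then be expected even if that syndrome had no biological correlate. The study could not tell such a list from the validation it is looking for.

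The interim raises a second, conditional problem. Its trigger is enrolment (50% of 15,000 = 7,500 patients), not outcome information. The first follow-up visit is at 12 months, and Table 2 allows 1 to 3 years before surveillance colonoscopy for patients with one or two small tubular adenomas. How much outcome information exists when the 7,500th patient is enrolled depends on a recruitment rate that the article does not give. If associations with outcome were tested then, an early result from immature data would be judged by the same 0.05 as the final one.

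**Working it through.** **1. The plan's own use of 0.05.** Section 2.3.6 uses N = (Zα/2 + Zβ)² × P(1−P)/d², with 1.96 and 1.28, so (3.24)² = 10.4976.

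- Recurrence, P = 0.58, d = 0.02: 10.4976 × 0.58 × 0.42 / 0.0004 = 6,393.04, rounded up to 6,394. The plan states: "Using an absolute error of 2%, the minimum sample size calculation yielded 6,394 cases". With 20% loss, 6,394/0.8 = 7,992.5, so 7,993, as stated.
- Cancer, P = 0.0035, d = 0.00175: 10.4976 × 0.0035 × 0.9965 / 0.00175² = 11,955.3, so 11,956 (11,967 with unrounded normal quantiles). The plan states 11,970, close enough to count as reproduced. 11,970/0.8 = 14,962.5, so 14,963, as stated.

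Each outcome is sized with the full 0.05. The formula sets a margin of error around one rate and names no comparison between groups.

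**2. Screening.** For m true null hypotheses each tested at 0.05, the expected number of false positives is 0.05m. The chance of at least one, if the tests are independent, is 1 − 0.95^m. The article gives no feature counts, so m is assumed:

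| Null tests m | Expected false positives | Chance of at least one |
|---|---|---|
| 20 | 1 | 64.2% |
| 59 | 2.95 | 95.2% |
| 100 | 5 | 99.4% |
| 1,000 | 50 | >99.9% |
| 5,000 | 250 | >99.9% |

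These are per contrast. Section 2.3.10 names three syndromes, which gives three pairwise contrasts. At 1,000 null features the expected total is 3 × 50 = 150. Correlation between features lowers the chance of at least one error but leaves the expected count unchanged.

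**3. What false-discovery control would do.** Benjamini-Hochberg at 5% over 1,000 features compares the smallest P-value with 0.05/1,000 = 0.00005 and relaxes the limit as more features pass. If no feature has a true association and the tests are independent, the chance of any declaration is 5% instead of near 100%.

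**4. Interim, only if outcomes are tested there.** With a two-sided 1.96 at both looks, the error is 1 − P(|Z1| ≤ 1.96 and |Z2| ≤ 1.96), where the two statistics have correlation √t and t is the information fraction at the interim:

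| t | Type I error per outcome |
|---|---|
| 0.05 | 9.6% |
| 0.10 | 9.5% |
| 0.25 | 9.1% |
| 0.50 | 8.3% |
| 0.75 | 7.3% |

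Because the trigger is enrolment, t is unknown and may be well below one half. The range is therefore more informative than the value at one half.

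**The case against.** The strongest reply is that this is a condensed article and an analysis plan may exist. False-discovery procedures and interim boundaries commonly sit there, and omics pipelines often apply them by default. The sentence does not say that the P-values are unadjusted, so a 0.05 threshold on adjusted P-values would be consistent with it. Parts of the text are also worded as exploration, including the multivariable models and the interaction networks. This stands to a degree: how results will finally be reported cannot be known from the article. It does not remove the point, which rests on a rule stated for all tests and not on silence. A reader who follows the text would apply 0.05 feature by feature, and the same section gives validation as the aim of the omics work.

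A reader might infer more than the documents support:

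- **That false positives are near certain for every claim, including the primary outcomes.** This holds only for a large screening family, and the size of that family is assumed.
- **That the two primary outcomes carry a family-wise error of 1 − 0.95² = 9.75%.** This needs one confirmatory test per outcome, and independence between them. The article names no primary between-group test and sizes both outcomes on precision around a single rate.
- **That the interim inflates type I error to 8.3%.** This assumes that outcomes are tested at the interim, and at exactly half the information. The article says neither.
- **That each tongue, pulse or constitution feature will be tested separately.** Sections 2.3.8 and 2.3.10 do not specify such tests.

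**Conclusion.** The point holds for the screening analyses, and conditionally for the interim. As written, about 5% of null features would be declared significant in analyses meant to support the validity of TCM classification. The 5% follows directly from the rule. The counts of 50 and 250 depend on assumed screens of 1,000 and 5,000 features, but under independence the conclusion that at least one false positive is very likely needs only about 59 null tests. For the interim, the size is about 7% to 10% per outcome if outcomes are tested at 0.05 at both looks, and there is no inflation if they are not. The text leaves open which applies.

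Adjustment across the two primary outcomes is optional here, for want of a named primary comparison. The point does not threaten the cohort or its data. It limits what can be claimed from the screening results, and it should be settled before those analyses are run.

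**What to change.** Replace the blanket sentence in section 2.3.10 with wording that does four things:

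1. States that P<0.05 does not apply to screening analyses.
2. Applies Benjamini-Hochberg control at a 5% false discovery rate within each omics platform, and within each family of TCM features that is tested (syndrome, constitution, tongue, pulse).
3. Reports subgroup and interaction results as estimates with confidence intervals, labelled exploratory.
4. States, here and in section 2.3.6, that the interim is descriptive (recruitment, data quality, completeness of follow-up) and includes no association tests.

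If the analysis plan already contains such rules, the article's sentence should be brought into line with them.

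The cost is fewer nominally significant exploratory results. None of the four changes alters the sample size. Splitting alpha across the two primary outcomes would not be free. At 0.025 each, the plan's formula for cancer gives (2.2414 + 1.2816)² × 0.0035 × 0.9965 / 0.00175² = 14,135, or 17,669 after 20% loss, against a target of 15,000. That formula concerns a single rate, so the figure only illustrates the direction. It is a reason to leave that adjustment to the sponsor's judgement.
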